### Sample size calculation

Most previous studies have based sample size calculations on differences of the intubation difficulty score (IDS), developed by Adnet in 1997 for direct laryngoscopy [12]. However, a retrospective study by McElwain has raised concerns about the validity of the IDS with VLS [13]. The most important outcome parameter for VLS or any guided intubation devices is the success rate. Most available data are from patients with normal airway anatomy and, therefore, not comparable with our setting. Only one study immobilized the patients’ necks with collars to investigate the C-MAC in 43 patients. That study found an overall success rate of 88% [10]. This is an unacceptable low success rate for the management of a difficult airway, but the study was underpowered: we calculated the 95% CI in that study to be 0.75 to 0.95 for overall success rate.

In order to rate an intubation device as “successful”, we define that the lower limit of the 95% CI should not be smaller than 0.9. We based our sample size on these values, congruent with our findings in a small pilot sample. We calculated the necessary sample size to obtain a distance of 0.05 to the expected success rate of 0.95, provided a probability of 0.95 and a power of 80% (SAS v.9.1, SAS Institute Inc., Cary, NC, USA). A total of 107 patients per device are necessary for this lower limit of 0.9. A total of 642 (6 × 107) patients will be necessary based on these assumptions, which leads us to include 720 patients to compensate for dropouts or missing data.

Secondary endpoints include parametric data, such as time necessary until success. Time until success has varied widely among different devices in published studies. Furthermore, that parameter seems to be influenced by the anesthesia provider. Therefore, we based our sample size calculation on first attempt success rate.

Because available data about our primary outcome, the first attempt success rate in a simulated difficult airway scenario, are scarce, we will recalculate sample size after the first 120 patients, based upon the values obtained from the first 20 patients for each device. In order to reduce bias, all participating investigators will remain unaware of results obtained from these 120 patients.

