#### Allocation of patients

Patients with written informed consent are randomly allocated to one of the six devices. The allocation sequence will be generated using online randomization software (http://randomization.com) in blocks of 30 intubations for the devices and stratified for each participating center and for each physician. The allocation will be concealed in sealed, opaque, sequentially numbered envelopes and will not be opened until the patient is anesthetized.

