### Potential problems and limitations

Because sample size has been calculated based on relatively vague figures, some adjustments in the total, necessary sample size may have to be incorporated when we re-calculate our sample size after the first 120 patients as per protocol. However, the statistical calculation is sound, and our assumptions are based on highly probable clinical expectations. Furthermore, the results of our study will be of clinical relevance regardless of whether our primary hypothesis will be confirmed or not and the much-feared “negative results” should be of no concerns in this study.

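### Recalculating N from first-attempt success in about 20 patients per device lets sampling noise set the sample size; the look should not be able to lower N below 120 per device

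*Protocol article*

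**What the plan says.** Under Sample size calculation, the protocol article says that data on first-attempt success in this scenario are scarce and that "we will recalculate sample size after the first 120 patients", "based upon the values obtained from the first 20 patients for each device". The safeguard given is that "all participating investigators will remain unaware of results obtained from these 120 patients". The Discussion (Potential problems and limitations) expects that the total may need adjusting "when we re-calculate our sample size after the first 120 patients as per protocol".

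The criterion for each device is fixed: "we define that the lower limit of the 95% CI should not be smaller than 0.9". Statistical analysis applies it to each laryngoscope separately. The planned size is 107 per device, 642 in all, raised to 720 (120 per device) for dropouts and missing data. It comes from a calculation "to obtain a distance of 0.05 to the expected success rate of 0.95", with a confidence level of 0.95 and 80% power.

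The article states no lower bound, no upper bound and no rule for turning the early results into a new N.

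**The concern.** Sample size re-estimation is usually harmless when it updates a nuisance quantity, such as a variance or a dropout rate. Here the only primary-outcome quantity available at the look is the success rate, and against a fixed benchmark of 0.90 that rate is the effect itself. The recalculation therefore reacts to an early estimate of the effect, taken from very few patients.

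Two things are at stake. The new N may be decided by chance, with identical devices pointing in opposite directions. And if a device that starts with a run of successes can be given fewer patients, the early luck is locked into a final 95% interval that makes no allowance for it.

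**Working it through.** **Inputs.** Benchmark 0.90, expected rate 0.95, distance 0.05, 95% confidence, 80% power, 107 and 120 per device, and 20 patients per device at the look (all from Sample size calculation). Six devices, each tested separately (Statistical analysis).

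**The plan's own figure.** 107 is reproduced closely as a precision calculation. The smallest n for which the 95% CI half-width is at most 0.05 with probability 0.80, at a true rate of 0.95, is 104 (Wilson) or 109 (Agresti-Coull). It is not reproduced as 80% power for a lower limit of at least 0.90. The score formula

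n = [(1.96·√(0.9·0.1) + 0.8416·√(p(1−p))) / (p − 0.9)]²

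gives, at p = 0.95, [(0.588 + 0.183)/0.05]² ≈ 238.

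**What 20 patients can show.** 19/20 has an exact 95% CI of 0.751 to 0.999. If the true rate is 0.95, with X ~ Binomial(20, 0.95):

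| Result | Probability, one device | At least one of six | n from the score formula |
|---|---|---|---|
| 18/20 or fewer | 0.264 | 1 − 0.736⁶ = 0.84 | none (estimate not above 0.90) |
| 19/20 | 0.377 | – | about 238 |
| 20/20 | 0.95²⁰ = 0.358 | 1 − 0.642⁶ = 0.93 | (0.588/0.10)² ≈ 35 |

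Both extremes occur in the same trial with probability 1 − 0.736⁶ − 0.642⁶ + 0.377⁶ ≈ 0.77, although the six devices are identical. At lower true rates, P(18/20 or fewer) per device is 0.41 (true 0.93), 0.61 (0.90) and 0.71 (0.88).

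**If the distance calculation is repeated instead.** With the Wald form n = 1.96²·p(1−p)/0.05², an observed 0.90 gives 139 and 0.85 gives 196. These are finite, but they fix a distance of 0.05 around a rate at or below the benchmark, so they do not serve a lower limit of 0.90. An observed 1.00 gives 0.

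**Error rate at true 0.90.** The article gives no adaptation rule, so the rules below are assumptions. For a rule that sets N(s) after s successes in 20, and a cut-off c(N) at which the final two-sided 95% lower limit first reaches 0.90:

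error = Σ P(S = s) · P(Y ≥ c(N(s)) − s), where S ~ Binomial(20, 0.90) and Y ~ Binomial(N(s) − 20, 0.90).

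The nominal one-sided level is 2.5%. With fixed n the error is 1.45% at 107 and 1.6% at 120 (Wilson or exact limit). In the table, 19/20 leads to 238, and 18/20 or fewer leads to 120 or 300 (the two ends of each range):

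| N after 20/20 | Error, Wilson limit |
|---|---|
| 34 | 0.9–1.2% |
| 35 | 3.4–3.7% |
| 45 | 1.8–2.1% |
| 54 | 2.5–2.9% |
| 64 | 1.6–1.9% |
| 120 (no decrease) | 1.6–1.9% |

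The jump at 35 arises because 35/35 is the first perfect score to pass the Wilson limit; it contributes 0.9³⁵ = 2.5% by itself. With an exact limit, 35/35 does not pass and the error at 35 is 0.9–1.2%. The exact limit first passes at 36/36, which adds 0.9³⁶ = 2.3% and gives about 3.2–3.5%.

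**The case against.** The strongest reply is that much of the harm depends on a rule the article never states. That is right, and it limits the point in five ways.

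- **Error rate.** A reader might infer that the plan inflates the type I error. The article specifies no decrease, no device-specific N and no extension size, and the Discussion speaks of the total. The highest figures need a cut to about 35, which also sits badly with the 64 per group the article requires for its secondary outcome; at 64 the same rule stays below 2.5%. Inflation is possible, not established.
- **No solution.** A reader might infer that following the plan yields an infinite N. That holds for power against 0.90. Repeating the 0.05-distance calculation always returns a number, though one that does not serve the stated criterion.
- **Safeguards.** A reader might infer an open look with no protection. Investigators are kept unaware of the results, which limits operational bias. A floor or an adjustment may also stand in the full protocol or analysis plan, which are not shown. Neither would add information to 20 patients.
- **Pooling.** Had the six devices been pooled (120 patients), an estimate at or below 0.90 would occur in only 1.7% of trials at a true 0.95. The text says for each device, however, and the devices are judged separately.
- **Allocation.** Randomization is "in blocks of 30 intubations for the devices", stratified by center and physician, so 120 patients need not hold exactly 20 per device. Assuming 12 physicians with 10 patients each, counts run from about 15 to 25. This hardly changes the recalculation and is minor.

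**Conclusion.** The point holds in a limited form. The stated basis for the recalculation, about 20 patients per device, is too small to guide N, and the rate it uses is the effect under test. Even if the planning value of 0.95 is true for all six devices, 84% of trials would have at least one device at 18/20 or fewer and 93% at least one at 20/20. These are exact binomial results that need only independent patients and 20 per device.

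The error-rate part is conditional. If N may fall after early success, the one-sided error at a true 0.90 can reach about 3.7% under some of the assumed rules. With no decrease below 120 it is 1.6–1.9% for the extensions tested. A floor does not guarantee 2.5% for every conceivable extension: with n never below 107, the least favorable rule reaches about 3%.

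A reader might also infer that the recalculation should simply be deleted. That is debatable: at 120 per device and a true 0.95, the chance of a lower limit of at least 0.90 is only about 44% (Wilson or exact), so a way to raise N has some value.

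**What to change.** In Sample size calculation and in Potential problems and limitations, state that:

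1. the 120-patient look cannot reduce N below 120 per device (720 in total);
2. any change gives one common N for all six devices and is determined by a statistician outside the study team;
3. the look serves mainly to check the share of patients without an evaluable primary outcome, against the allowance of (720 − 642)/720 = 10.8%.

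The cost is amendment wording; fewer than 10 patients had been enrolled at submission. The downside is that N cannot be reduced when early success is high, and early device-specific rates no longer drive N. The change does not by itself raise the 44% chance noted above.

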We will compare time to intubate in unguided vs. guided VLS as the secondary outcome. There are not sufficient data available to calculate sample size for this secondary outcome parameter. Therefore, we base our sample size calculation on effect size: based on an estimated medium effect size (Cohen’s d of 0.5; assuming normal distribution), 64 samples per group are necessary, given a 0.05 level (*P* = 0.05) and 80% power. Because our primary outcome requires 107 patients per group, we are well within the necessary sample size even for this secondary outcome parameter.

Experience with the device is expected to be a major confounding factor. Only a limited number of experienced anesthesiologists at each study center will perform the intubation. To avoid a learning curve bias and to minimize variation in the performance, only anesthesiologists who have intubated patients without any airway pathology several times with each device until they feel competent with the devices will participate. We did not set *a priori* a fixed figure of intubations for each device because the individual experience with different devices is very divergent between the study centers and the participating anesthesiologists. Ideally, experience with the device should be equal, and prior experience will be recorded. We limit participants per center to a maximum of four physicians.

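### The run-in is credited with avoiding learning-curve bias, but it cannot equalise device experience, and the named tests ignore recorded experience and the physician strata

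*Protocol article*

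**What the plan says.** The Sample size calculation section of the protocol article states: "Experience with the device is expected to be a major confounding factor". To deal with this it restricts the operators: "only anesthesiologists who have intubated patients without any airway pathology several times with each device until they feel competent with the devices will participate". It sets no number of practice uses, on the ground that "the individual experience with different devices is very divergent between the study centers and the participating anesthesiologists". It adds: "Ideally, experience with the device should be equal, and prior experience will be recorded". It also caps the operators: "We limit participants per center to a maximum of four physicians". The stated purpose of these measures is to avoid learning-curve bias and to limit variation in performance.

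Under Allocation of patients, randomization is "in blocks of 30 intubations for the devices and stratified for each participating center and for each physician".

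Under Statistical analysis, the primary outcome is each device's own 95% confidence interval set against 0.9. Secondary outcomes are compared by chi-square or Fisher's exact test, ANOVA or Kruskal-Wallis, and Student's t or Mann-Whitney. Time to success is compared a priori between unguided and guided devices. Operator, center, prior experience and case order have no stated role in any of these analyses.

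**The concern.** Two things do not fit together. First, experience described as very divergent cannot be made equal by a threshold that each operator sets for himself or herself. The practice cases are patients without airway pathology, whereas the trial task is a collared, taped airway with mouth opening aimed at 20 to 25 mm (Clinical study procedure). Practice with the collar is neither required nor ruled out. Second, the confounder is named and measured, and operators are a randomization stratum, yet the tests named for the comparative outcomes use none of this.

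The primary conclusion is an absolute pass or fail per device against 0.9. Early, less practised uses of a device count fully in that verdict, and no reference arm absorbs them. The guided-versus-unguided contrasts in success and time can also carry differences in how well the operators know the devices.

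**Working it through.** **What the safeguards balance**

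| Safeguard | Balances | Leaves open |
|---|---|---|
| Stratification by center and physician | The same operators use every device, so general skill is shared | An operator's familiarity with one device compared with another |
| At most four physicians per center | Limits the number of operators | Each operator's starting experience |
| Self-judged run-in with every device | Some prior use of each device | A common level, and experience of the trial task |
| Recording of prior experience | Makes an analysis possible | No analysis using it is named |

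**Inputs from the protocol article.** 3 centers; at most 4 physicians per center; 6 devices; 720 patients; expected success 0.95; benchmark 0.9; 95% confidence interval.

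**The plan's own figure.** 107 per device is reproduced exactly as the smallest n for which a one-sided 95% Clopper-Pearson lower limit reaches 0.90 when the observed rate is 0.95 (0.90005 at n = 107, 0.89974 at n = 106). With the allowance for dropout, 720/6 = 120 per device. The illustration uses 120.

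**Uses per operator and device**
- 12 operators (3 × 4, the maximum): 720/12 = 60 cases each; 60/6 = 10 per device.
- 6 operators: 720/6 = 120 cases each; 120/6 = 20 per device.

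**Pass mark at n = 120.** The two-sided 95% Wilson lower limit is 0.906 for 115 successes and 0.895 for 114, so 115 are needed. Clopper-Pearson gives the same mark. Wald needs 114.

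**Illustration.** Assumptions that the documents do not supply: a plateau success of 0.95, and a lower rate in the first 3 uses per operator and device.
- Deficit of 5 points, 10 uses: 0.3 × 0.90 + 0.7 × 0.95 = 0.935.
- Deficit of 10 points, 10 uses: 0.3 × 0.85 + 0.7 × 0.95 = 0.92.
- Deficit of 10 points, 20 uses: 0.15 × 0.85 + 0.85 × 0.95 = 0.935.

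Chance of passing, by exact binomial at the average rate:

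| Average success | Wilson, 115 or more | Wald, 114 or more |
|---|---|---|
| 0.95 | 0.442 | 0.606 |
| 0.935 | 0.201 | 0.331 |
| 0.92 | 0.075 | 0.147 |

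Modelling the two phases as separate binomials changes little: for 10 uses, 0.200 in place of 0.201 and 0.072 in place of 0.075.

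**Could the later uses carry a verdict of their own?** With 12 operators, uses 4 to 10 give 12 × 7 = 84 per device. The Wilson limit then needs 81 of 84 (lower limit 0.9002), and at a true 0.95 the chance of reaching it is only 0.39. That is too few for a separate verdict.

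**The case against.** The protocol discloses the problem and acts on it. It names the confounder, restricts the work to experienced anesthesiologists who have used every device, caps their number, records their experience, stratifies by physician, and explains why no fixed number was set. A common minimum would not equalise experience either, because the starting points differ. All this stands, and it is why no numeric minimum is asked for here.

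A statistical analysis plan that is not shown may contain adjusted analyses. That is possible, so the absence of covariate detail is not the point. The point is what the article does fix: a list of unadjusted tests, and a claim about the run-in that its own description does not support.

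A reader might infer three stronger things that the documents do not support.
- That the practice cases were uncollared. The text speaks only of absent airway pathology. Trial patients, too, are selected without known or presumed difficult airways before the collar is fitted. The article also mentions a pilot sample and an earlier collar study by the group, without saying who took part.
- That particular devices are disadvantaged, because GlideScope is called widely used and King Vision and McGrath MAC have no randomized trials. Those remarks concern the market and the literature, not these operators. King Vision is guided and McGrath MAC unguided, so they give no direction for that contrast.
- That the fall in the pass chance measures the actual bias. It rests on an assumed deficit. The 44% without any learning effect already reflects a separate question of power.

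**Conclusion.** The point holds in a limited form. The run-in may reduce learning-curve bias, but nothing in its description lets it avoid that bias, and physician strata do not balance familiarity by device. The tests named for the comparative outcomes ignore both the strata and the recorded experience.

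Whether a bias exists, how large it is and which device it affects cannot be told from the document. The illustration shows only that the per-device verdict is sensitive: a drop of 1.5 to 3 points in average success is enough to cut the chance of passing from 44% to between 20% and 7.5% (Wilson), or from 61% to between 33% and 15% (Wald). It assumes a plateau of 0.95, 120 analysed patients per device and independent outcomes. The claim that the results cannot be attributed to the devices at all would go too far. The improvement is worth making because it uses data that the trial collects anyway.

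**What to change.** 1. Leave the primary per-device rule as it is, on all randomized patients.
2. For guided versus unguided success and time, replace the unadjusted tests by models that include physician nested in center, or add such models beside them.
3. Pre-specify a supportive version of these models that adds recorded prior experience with the allocated device and the within-trial sequence number of that operator's uses of that device.
4. Report first-attempt success per device for early and later uses (for example 1 to 3, and 4 onward) as descriptive support only. Do not give a failed device a second verdict or a softer label on that basis.
5. Reword the claim so that the run-in is said to reduce learning-curve bias, and state that the per-device verdicts apply to operators with the recorded level of experience.

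**Cost.** A little extra analysis, and early and late estimates that will be imprecise. Prior experience is already to be recorded and physician is a stratum; the order of each operator's cases should follow from the sequentially numbered allocation. No change to recruitment is needed. Fewer than 10 patients had been enrolled when the article was submitted (Trial status), so at that point the analyses could still be fixed in advance.

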### Statistical analysis

For the primary outcome, it will be analyzed for each laryngoscope whether the 95% confidence interval of its primary success is below 0.9. For the secondary outcome parameters, the data distribution will determine which statistical test will be used. For frequencies (for example, number of required manipulations, overall attempt success, complications) chi-square test or Fisher’s exact test will be used. Parametric data will be analyzed using ANOVA; for non-parametric continuous data Kruskal-Wallis test will be used. For comparison between two devices, we will use Student’s *t*-test and Mann-Whitney’s *u*-test, as appropriate. We will do *a priori* comparisons of the time necessary until success between the unguided VLS and any of the guided VLS.

Data will be presented as mean with standard deviation, median and interquartile range, or number and percent. Effect sizes (with 95% CI) will be reported as Cohen’s d for interval data and as odds ratio for proportions. A probability of 0.05 is considered as statistically significant.

The patient flow diagram according CONSORT guidelines is provided in Figure 1.

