#### Clinical study procedure

Premedication will be according to the standard operating procedures of the participating centers. Standard non-invasive monitoring includes ECG, non-invasive arterial blood pressure, oxygen saturation (SpO_2_), end-tidal CO_2_ and volatile anesthetic level if applicable. A bispectral index (BIS, Aspect Medical Systems, Norwood, MA, USA) or a different processed EEG monitoring will be used whenever available. Anesthesia will be induced with propofol 1.5 to 3 mg/kg body weight and fentanyl 1 to 2 mcg/kg body weight. After facemask ventilation is established, neuromuscular blocking agents (rocuronium 0.6 mg/kg body weight) will be given and appropriate action monitored by neuro-stimulation. The inter-incisor distance at maximum mouth opening will be measured while the patient is asleep. Then, the extrication collar (Stifneck™, Laerdal, Copenhagen, Denmark) will be properly adjusted, and a self-adhesive tape will be used to fix the head on the operating table, as done in an earlier study by our group [6]. The inter-incisor distance will be measured at maximal mouth opening aiming at a mouth opening between 20 to 25 mm.

If mask ventilation remains adequate and a sufficient level of anesthesia is confirmed (BIS <55, stable hemodynamic parameters, unresponsiveness to jaw thrust), the tracheal intubation will be performed with the help of one of the six VLS, according to randomization.

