#### Definition of time

Time necessary until success is measured from the time the facemask is taken away from the face until the end-tidal CO_2_ curve appears on the monitor of the respirator. Time for each attempt is measured separately.

Cormack-Lehane (CL) grade [14] at laryngoscopy (not developed for indirect laryngoscopy, but necessary for the calculation of the IDS).

Inter-incisor distance before induction of anesthesia and after placement of the collar to measure maximum mouth opening and the reduction of mouth opening by the collar (collar adjusted to permit a minimal opening of 18 mm, according to the minimal requirements for Airtraq and King Vision)

Number of optimization maneuvers required (cricoid pressure or BURP, backward, upward, rightward pressure), second assistant, adjustment of head positioning) to aid tracheal intubation [15].

View on the glottic opening in percent (%) as judged by the operator: Percentage of Glottic Opening (POGO) Score [16].

Adverse events: cardiovascular extremes: any hypo-/ hypertension and tachycardia/ bradycardia exceeding 20% from baseline. Blood on device, and injury during intubation attempt, suspicion of aspiration/regurgitation (gastric fluid in the ventilation tube or in the hypopharynx), hypoxia (SpO_2_ <90%), bronchospasm, airway obstruction or any other form of stridor, coughing, dental, tongue or lip trauma.

Technical problems with the device, such as fogging, impeded vision and monitor/light source failure.

The Intubation Difficulty Scale (IDS) score will be calculated as previously published [12], using the following parameters: number of attempts and operators, alternative techniques, Cormack-Lehane grade, lifting force, laryngeal pressure and vocal cord mobility.

Demographic and perioperative data: sex, age, weight and body mass index, dentition, surgical procedure/ duration, duration of anesthesia, date/ time of hospital discharge.

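### Time until success is compared with unadjusted tests only, although sex, body mass index and mouth opening are recorded; some precision is lost to the extent that these are prognostic, probably a modest amount

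*Protocol article*

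**What the plan says.** Under Statistical analysis in the protocol article, the rule for secondary outcomes is that "the data distribution will determine which statistical test will be used". For more than two devices: "Parametric data will be analyzed using ANOVA; for non-parametric continuous data Kruskal-Wallis test will be used". For pairs: "For comparison between two devices, we will use Student’s" t-test or the Mann-Whitney test. Effect sizes are to be reported with 95% confidence intervals. No covariate, regression model or stratified test is named.

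The variables that could serve as covariates are already collected. The measurement list under Definition of time includes "Demographic and perioperative data: sex, age, weight and body mass index, dentition", and also mouth opening (inter-incisor distance) before and after the collar. Patient population excludes patients with BMI above 35 kg/m² or an inter-incisor distance below 3.5 cm as known or presumed difficult airways. Tube size differs by sex, and so does the Airtraq blade size.

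Allocation of patients stratifies randomisation by centre and physician. Sample size calculation says that time appears to depend on the anesthesia provider and expects device experience to be a major confounder. The named tests use none of these factors.

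**The concern.** If sex, BMI or mouth opening explain part of the variation in time until success, an unadjusted test leaves that part in the error term. Intervals around device differences are then wider than the collected data require, and small differences are harder to detect. Time is the main secondary outcome, with its own hypothesis (guided against unguided devices). Baseline adjustment needs no new measurement.

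The article names the tests outright, so this is a stated method and not a detail left open. A later analysis plan with an adjusted main analysis would depart from it.

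**Working it through.** **Inputs from the article.** Two-sided alpha 0.05, 80% power, and for time "based on an estimated medium effect size (Cohen’s d of 0.5; assuming normal distribution", giving "64 samples per group are necessary, given a 0.05 level". The primary outcome sets 107 evaluable patients per device, so a pooled guided-against-unguided comparison has 3 × 107 = 321 per class.

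**Input that must be assumed.** R-squared, the share of outcome variance explained by the patient covariates. The article gives none; 2%, 5%, 10% and 20% are used.

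**1. The plan's own figure.** n per group = 2(1.960 + 0.842)² / 0.5² = 62.8, so 63 by the normal approximation. The t-based calculation gives 63.77, so 64. The stated 64 reproduces.

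**2. Unadjusted power at the planned size.** For d = 0.5, the t-based power is 95.4% at 107 per device and above 99.99% at 321 per class. For d = 0.30 at 107 per device it is 58.9%.

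**3. Effect of adjustment.** Residual SD becomes √(1 − R²) times the unadjusted SD. Hence:
- interval width changes by the factor √(1 − R²);
- the equivalent gain in patients is 1/(1 − R²) − 1;
- power follows from replacing d by d/√(1 − R²). For example, R² = 10% turns 0.30 into 0.30/√0.90 = 0.316.

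| Assumed R² | Interval narrower by | Equivalent extra patients | Power, d = 0.30, 107 per device | Power, d = 0.5, 107 per device |
|---|---|---|---|---|
| 0 | – | – | 58.9% | 95.4% |
| 2% | 1.0% | 2.0% | 59.7% | 95.7% |
| 5% | 2.5% | 5.3% | 61.1% | 96.2% |
| 10% | 5.1% | 11.1% | 63.4% | 97.0% |
| 20% | 10.6% | 25.0% | 68.5% | 98.3% |

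For the pooled comparison at d = 0.20 (321 per class), power goes from 71.6% to 73.8%, 76.0% and 80.7% at R² of 5%, 10% and 20%.

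**4. What adjustment costs.** Three centres with at most four physicians each give at most 12 physicians. If each works at one centre, physician effects include centre and use at most 11 degrees of freedom. Sex and BMI add 2. With 642 evaluable patients and 6 devices, residual degrees of freedom fall from 636 to 636 − 13 = 623. This is negligible.

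**5. Chance imbalance in sex.** If half the patients are women (assumed), the SD of the difference in the share of women between two devices is √(2 × 0.25/107) = 0.068, about 7 points. If sex shifted time by 0.3 SD (assumed), such an imbalance would move the contrast by 0.3 × 0.068 = 0.02 SD. The standard error of the contrast is √(2/107) = 0.14 SD.

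**6. Mouth opening as a covariate.** Clinical study procedure says "The inter-incisor distance at maximum mouth opening will be measured while the patient is asleep", before the collar is fitted. The measurement list under Definition of time places the pre-collar value before induction. The two do not agree. The envelope stays sealed only until the patient is anesthetized, so a measurement taken asleep could follow knowledge of the device.

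**The case against.** Unadjusted tests are valid in a randomised trial, and covariate choice for secondary outcomes is often settled in an analysis plan that is not shown here. Nowhere does the article say that sex, BMI or mouth opening predict intubation time or glottic view. It uses BMI and mouth opening only to exclude patients, and those exclusions narrow their range. The collar then aims at an opening of 20 to 25 mm in everyone, which removes much of the baseline difference. The factors that the article itself ties to time are the provider and experience. The d = 0.5 it plans for is amply powered.

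Most of this stands, and it limits the size of the point. A low R-squared is plausible for BMI and mouth opening, and any adjusted model should include centre and physician before the patient covariates. Two things remain. The article commits to unadjusted methods instead of leaving the matter open. And d = 0.5 is a conventional value, adopted because data were lacking, so good power at 0.5 does not make precision irrelevant for smaller differences.

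A reader might infer that a definite amount of precision is being wasted, that the comparison of time is underpowered, or that uneven numbers of women could distort it. The article does not support these readings. No R-squared is given; power at the planned effect is about 95% or higher; and chance imbalance in sex is already covered by the type I error and is small beside the standard error. A reader might also conclude that glottic view should move to a linear model. That is debatable for a score bounded between 0% and 100%.

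**Conclusion.** The point holds as an efficiency matter for time until success. The named tests are unadjusted, suitable baseline variables are on file, and precision is lost to the extent that they are prognostic. Interval narrowing is about 1% to 5% for R-squared of 2% to 10%, and about 11% at 20%. These R-squared values are assumptions. The power figures also assume normally distributed outcomes compared by t-test; no gain over the rank tests has been calculated. The possible gain from modelling centre and physician is not included, because the article gives no figure for it. The primary outcome and detection of the planned d = 0.5 do not change.

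**What to change.** In the Statistical analysis section:

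- **Time until success:** prespecify a linear model for log time with device, the randomisation strata (centre and physician), sex and BMI. Keep the unadjusted test as supportive.
- **Mouth opening:** reconcile the timing of the pre-collar measurement between Clinical study procedure and the measurement list. Add it to the model only if it is taken before the allocation envelope is opened.
- **Glottic view (POGO score):** keep the rank-based test as the main analysis, with any adjusted model as supportive.

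The cost is a change of wording, slightly more analysis work and a few degrees of freedom. Sex and BMI are already collected. Trial status reports fewer than 10 patients enrolled at submission, so at that stage the change could be made before any comparative results were known.
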